### Statistical Analyses for Immune Measurements

The initial statistical approach will include a descriptive cross-sectional analysis at each timepoint, both for quality assurance and to attain a better understanding of the distributions of the immune cell and cytokine profile variables for use in subsequent analyses, including the need for any transformations (ie, logarithmic transformation to symmetrize the residuals). Factor analysis will be employed as a means of data reduction to probe latent cytokine profiles reflected across the manifest indicators (eg, tumor necrosis factor-α, IL-6, IL-1β). We will first compare levels of a combined score of peripheral innate immune cytokines and frequency of maternal immune cells between women who do and do not develop PMADs in separate models to evaluate cross-sectional effects, employing a multivariable linear regression model to adjust for relevant covariates (eg, gestational age, BMI). Similar models will be repeated for maternal cytokines and innate cell recruiting factors as produced by the stimulated cells. Second, we will test whether the magnitude of group difference varies across the study period in a longitudinal analysis. We will fit a generalized linear population-average model estimated using generalized estimating equations with exchangeable working correlation structure to account for within-women correlation of mood measures. The model will include the relevant immune markers identified in the cross-sectional analyses, indicators for visit and group, as well as any relevant interaction terms (immune marker by group or immune marker by visit). The models will adjust for baseline severity of depressive symptoms and psychotropic medication use. Standard model checking will be performed, and the most parsimonious model will be selected based on the Akaike information criterion or quasi-likelihood information criterion for generalized estimating equations models. To test the within-group effects of severity of PMAD symptoms, the dichotomous group variable will be replaced by continuous Edinburgh Postpartum Depression Scale and Generalized Anxiety Disorder Scale-7 item scores in analytic models and restricted to only the subset of women with significant PMAD symptoms.

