Determine whether the use of a smart bassinet (SB) augments infant sleep and improves maternal sleep during the first 6 months post partum compared to the use of a traditional bassinet (TB). (1) Hypothesis 1a: Infants who sleep in SB will have better sleep (ie, diary and Brief Infant Sleep Questionnaire as maternally reported) [40] than those who sleep in TB. Outcomes will include maternally reported sleep duration, awakenings, as well as objectively assessed (actigraphy) wake after sleep onset and sleep onset latency. (2) Hypothesis 1b: Mothers of infants who sleep in SB will have better subjectively reported (ie, diary and Pittsburgh Sleep Quality Index) and objectively assessed (actigraphy) sleep compared to those of infants who sleep in TB. Outcomes will be the same as those for infants.Determine the effect of SB on maternal postpartum depressive and anxiety symptoms and evaluate the model that the association between SB and postpartum depressive symptoms is mediated by both infant and maternal sleep. (1) Hypothesis 2a: Mothers of infants who sleep in SB will have fewer postpartum depressive symptoms over time (ie, Edinburgh Postnatal Depression Scale) compared to those of infants who sleep in TB. (2) Hypothesis 2b: SB improves infant sleep, which then predicts better maternal sleep, and thereby predicts lower maternal depressive symptoms.Compare the trajectory of immune system function from late pregnancy through post partum between participants with and without PMADs and between SB and TB groups. (1) Hypothesis 3a: Peripheral cytokines, immune cells, and stimulated cytokine profiles of women with PMADs assessed in late pregnancy and at 3 and 6 months post partum will indicate greater innate immune activity compared to those of women without PMADs. (2) Hypothesis 3b: Mothers of infants who sleep in SB will exhibit lesser innate immune dysfunction than mothers of infants who sleep in TB.Exploratory aim: Evaluate whether the elevated risk demonstrated by previously identified PMAD epigenetic biomarkers at the TTC9B and HP1BP3 genes can be modified by using an SB. We hypothesize that the elevated risk will be reduced in the SB group compared to that in the TB group.

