#### Additional Factors to Consider and Use as Covariates

These include (1) presence of spouse/partner and other children at home [36,65-67]; (2) type of feeding [68-70]; (3) infant variables such as acid reflux, colic, and gestational age; (4) consistency of bedtime routine [71-73] and when moved to a crib; (5) history of childhood trauma in the mother via the Childhood Trauma Questionnaire [74], as prior trauma is highly correlated with depressive episodes, especially in new mothers [75,76] and negatively affects sleep [77]; and (6) type of delivery, complications, or time spent in neonatal intensive care unit.

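### The immune models that contrast women with and without PMADs name no term for randomised arm, so the 3- and 6-month PMAD–immune association can partly reflect the treatment effect

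*Protocol article*

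**What the plan says.** Hypothesis 3a (Introduction, third aim) compares immune profiles of women with and without PMADs in late pregnancy and at 3 and 6 months post partum. Statistical Analyses for Immune Measurements gives three analyses.

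- **Cross-sectional.** Markers are compared "between women who do and do not develop PMADs in separate models to evaluate cross-sectional effects". The covariates are given only by example, and arm is not among the examples.
- **Longitudinal.** A GEE model contains the relevant immune markers plus "indicators for visit and group, as well as any relevant interaction terms (immune marker by group or immune marker by visit". On adjustment: "The models will adjust for baseline severity of depressive symptoms and psychotropic medication use". Model choice is then by AIC or QIC.
- **Symptom severity.** "the dichotomous group variable will be replaced by continuous Edinburgh Postpartum Depression Scale and Generalized Anxiety Disorder Scale-7 item scores", in the subset of women with significant symptoms. This sentence is the best evidence that *group* means PMAD status and not treatment arm.

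The section Additional Factors to Consider and Use as Covariates has six headings, the first of which is "presence of spouse/partner and other children at home". Arm is not one of them.

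The same trial hypothesises that "Mothers of infants who sleep in SB will have fewer postpartum depressive symptoms over time" (2a) and that "Mothers of infants who sleep in SB will exhibit lesser innate immune dysfunction than mothers of infants who sleep in TB" (3b).

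The section Mean Differences separately assigns hypothesis 3a to model 4, one of the treatment-by-time MANOVA models.

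**The concern.** Arm is randomised, comes before every postpartum mood and marker value, and is expected by the plan to move both. In data pooled over the two arms, a variable of that kind can produce an association between PMAD status and a marker even where none exists within arm. If SB works as hypothesised, women with PMADs will come disproportionately from the traditional bassinet (TB) arm and will show more innate immune activity partly for that reason. The bias has the sign that hypothesis 3a predicts, so a positive finding could not be cleanly separated from the treatment effect.

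The longitudinal question is exposed as well. The bias is zero before delivery, when no bassinet is in use, and can be above zero afterwards. That pattern looks like a PMAD difference that grows over time, which is what the longitudinal analysis is meant to detect.

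Model 4 does not help. It contains arm but no PMAD factor, so it cannot test hypothesis 3a. The models that do contrast women by PMAD status are the ones that do not name arm.

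**Working it through.** **Inputs from the protocol article.** Pilot effect on depression d = 0.33, two-sided alpha 0.05 and 80% power (Power); 1:1 allocation (Study Design); 342 women (Participants) and 15% attrition (Missing Data), so 342 × 0.85 ≈ 291 evaluable; PMAD rates from 12.2% for spouses to 26% for active-duty women (Introduction).

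**Assumptions not in the article.** The SB effect on a marker, *e*, is taken as 0.2–0.5 SD. The d = 0.33 is applied as a shift in a normal liability for PMAD. There is no PMAD–marker association within arm.

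**Check of the plan's own figure.** Per arm, 2 × (1.960 + 0.842)² / 0.33² = 144.2, rounded up to 145, so 290 in total. The Power section gives 286, which agrees within 2%. The article gives no figure for hypothesis 3a itself.

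**Step 1: PMAD risk by arm.** The arms are placed 0.165 SD either side of the threshold. For a rate of 26% the threshold is z = 0.643.
- TB: 1 − Φ(0.643 − 0.165) = 0.316
- SB: 1 − Φ(0.643 + 0.165) = 0.209

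**Step 2: share of SB women.**
- With PMAD: 0.209 / (0.209 + 0.316) = 0.398
- Without PMAD: 0.791 / (0.791 + 0.684) = 0.536
- Difference: 0.138

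At a rate of 12.2% the risks are 0.159 (TB) and 0.092 (SB), the shares 0.366 and 0.519, and the difference 0.153.

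**Step 3: spurious PMAD difference** = difference in SB share × *e*. At 26% and *e* = 0.33: 0.138 × 0.33 = 0.045 SD.

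**Step 4: type I error.** With pooled PMAD proportion 0.263, SE = √(1/(291 × 0.263) + 1/(291 × 0.737)) = 0.133. Then δ = 0.0455/0.133 = 0.34, and Φ(δ − 1.96) + Φ(−δ − 1.96) = 6.3%.

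| PMAD rate | *e* = 0.20 | *e* = 0.27 | *e* = 0.33 | *e* = 0.50 |
|---|---|---|---|---|
| 12.2% | 0.031 SD, 5.3% | 0.041 SD, 5.6% | 0.050 SD, 5.9% | 0.076 SD, 7.2% |
| 26% | 0.028 SD, 5.5% | 0.037 SD, 5.9% | 0.045 SD, 6.3% | 0.069 SD, 8.1% |

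**Sensitivity.**
- *Protocol rate taken as the TB rate, full 0.33 shift in SB.* At 26% the SB risk is 16.5%, SB shares are 38.9% and 53.0%, and at *e* = 0.33 the bias is 0.047 SD with type I error 6.2%. Taking rates up to the 50% that the Introduction mentions and *e* from 0.2 to 0.5, the range is 0.03–0.08 SD and 5.3%–8.4%. With 393 × 0.85 ≈ 334 women, from the target in the Power section, the upper end is 8.9%.
- *Missing blood draws.* A further 7% loss leaves 342 × 0.85 × 0.93 ≈ 270. At 26% and *e* = 0.50, SE = √(1/(270 × 0.263) + 1/(270 × 0.737)) = 0.138, δ = 0.069/0.138 = 0.50, and the type I error is 7.9% instead of 8.1%.

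**Effect of the fix.** Linear regression was simulated (n = 290, 8,000 runs per setting; TB PMAD rates 12.2%, 26% and 50%; *e* = 0.33 and 0.50). Without arm the bias was 0.044–0.081 SD. With arm added it was −0.002 to +0.002 SD, with type I error 4.6%–5.1%.

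**The case against.** **Arm is unnamed, not excluded.** This stands for the cross-sectional models. Their list is open, the article is condensed, and a fuller document may name arm. It is weaker for the GEE model, whose terms and adjustment set are stated outright. Selection by AIC or QIC could also drop an optional arm term.

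**The meaning of *group* and the outcome are unclear in the GEE.** The working correlation is described as one among a woman's mood measurements, so mood appears to be the outcome and the markers predictors. A PMAD indicator would then be nearly circular. This stands in part. The calculation above is for a marker compared between PMAD groups at one visit and does not size the bias in the GEE. The argument itself carries over, because arm is expected to affect the marker as predictor and mood as outcome.

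**Arm need not be a confounder.** The abstract presents immune function as a physiological link between sleep and mood. If SB changes mood through immune function, the arm-related association is part of the PMAD–immune link and is not spurious. This stands as a condition on the claim. It does not argue against adjustment: arm is a randomised baseline variable and neither a mediator nor a collider, so including it does not over-adjust.

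**The effect is small.** This also stands. The top of the range needs a 0.5 SD effect on the marker, larger than any pilot effect in the Power section, including infant sleep at 0.39.

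A reader might infer that hypothesis 3a as a whole is confounded by the intervention. The documents do not support that: the late-pregnancy sample is taken before any bassinet is used, so arm cannot bias that contrast.

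**Conclusion.** The point holds for the 3- and 6-month PMAD contrasts, for the symptom-score versions at those visits, and for the change in the PMAD difference from late pregnancy. The models as described do not name randomised arm, although the plan's own hypotheses expect it to affect both sides of the association.

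The bias favours hypothesis 3a and is probably small: 0.03–0.08 SD and a type I error of 5.3%–8.1% over the assumed marker effects. The more plausible part of that range is 0.04–0.05 SD and 5.6%–6.3%, at marker effects of 0.27–0.33 SD, the size of the pilot effects on maternal sleep and depression.

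These figures rest on a marker effect that the article does not give, on reading d = 0.33 as a liability shift, and on SB acting on mood and markers by separate routes. They apply to the cross-sectional comparison and not to the GEE. The case for change is that the correction is specific and nearly free. The documents do not show that it would alter the trial's conclusions.

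**What to change.** 1. In Statistical Analyses for Immune Measurements, include randomised arm as a fixed term in every postpartum cross-sectional model that uses PMAD status or EPDS/GAD-7 scores.
2. In the longitudinal model, include arm and arm-by-visit as fixed terms, exempt from AIC/QIC selection.
3. Report the arm-adjusted PMAD–immune association as the result for hypothesis 3a.
4. Define *group* and name the outcome of the longitudinal model.
5. Reconcile Mean Differences with the immune section on how hypothesis 3a is tested, since model 4 has no PMAD factor.

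The cost is one parameter in each cross-sectional model and three in the longitudinal model (one for arm, two for arm-by-visit over three blood draws). Arm is known for every randomised woman, and no data collection changes. Recruitment began in January 2025 and analysis is expected to finish by July 2028, so there should be time to specify this in advance.

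### The longitudinal immune model contains no term that tests whether the PMAD versus no-PMAD difference in immune markers changes over visits, although that is its stated purpose

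*Protocol article*

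**What the plan says.** All references are to the protocol article.

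- **Aim (Introduction, third aim):** "Compare the trajectory of immune system function from late pregnancy through post partum between participants with and without PMADs and between SB and TB groups". This contains two comparisons: one by PMAD status and one by randomized arm.
- **Stated purpose (Statistical Analyses for Immune Measurements):** after cross-sectional models, "we will test whether the magnitude of group difference varies across the study period in a longitudinal analysis".
- **Model for that purpose (same section):** a population-average GEE model. "The model will include the relevant immune markers identified in the cross-sectional analyses, indicators for visit and group", together with "any relevant interaction terms (immune marker by group or immune marker by visit". The most parsimonious model is then chosen by AIC or QIC.
- **Apparent response:** the GEE uses an "exchangeable working correlation structure to account for within-women correlation of mood measures".
- **Meaning of group:** the preceding step compares immune levels "between women who do and do not develop PMADs in separate models to evaluate cross-sectional effects", and in a later step "the dichotomous group variable will be replaced by continuous Edinburgh Postpartum Depression Scale" and GAD-7 scores. Group is therefore PMAD status, not trial arm.
- **Blood sampling (Primary Maternal Assessments; Table 1):** enrollment, 3 months and 6 months post partum, which is three visits.

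**The concern.** Whether a group difference varies over visits is a group-by-visit question. The model written to answer it names two interactions, and neither is group by visit. The immune markers also sit on the predictor side, so the model does not estimate a group difference in immune markers at all.

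If the analysis is run as written, the PMAD-status half of the trajectory comparison has no test. There is also a reporting risk. A significant marker-by-visit term could be presented as evidence that the immune difference between women with and without PMADs changes over time, when it says only that the marker–mood association changes.

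**Working it through.** The article states no figure on this point, so there is none to reproduce. The check is to write out the model and see what each term can estimate.

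**Inputs.** Three blood-draw visits, a two-level group (PMAD yes/no), and one marker or factor score M for simplicity. G is group, and V2 and V3 indicate months 3 and 6.

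**1. The model as listed, mood as response**

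E(mood) = b0 + b1·M + b2·G + b3·V2 + b4·V3 + b5·M·G + b6·M·V2 + b7·M·V3

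This has 8 parameters.

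- Group difference at a given marker value m: b2 + b5·m. No visit term appears, so the difference is forced to be the same at all three visits.
- b5 asks whether the marker–mood slope differs between PMAD groups.
- b6 and b7 ask whether that slope differs between visits.

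No coefficient is a group difference in M, and none is a change in a group difference over visits.

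**2. Is group by visit implied by the listed terms?** It would add (2 − 1) × (3 − 1) = 2 columns. A numerical check on simulated data gave design rank 8 for the listed terms and 10 with group by visit added. The term is neither present nor implied.

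**3. Does adding group by visit to that model repair it?** The group difference becomes b2 + b5·m + c2·V2 + c3·V3, which is still a difference in mood. Testing c2 = c3 = 0 asks whether women classified by PMAD status differ in mood by a changing amount. That is close to circular and is not Aim 3's question.

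**4. The model that answers the stated question, marker as response**

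E(M) = a0 + a1·G + a2·V2 + a3·V3 + a4·G·V2 + a5·G·V3, plus covariates

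- Late pregnancy difference: a1
- Month 3 difference: a1 + a4
- Month 6 difference: a1 + a5
- Test that the difference does not vary: a4 = a5 = 0, on 2 df

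Both changes are needed. With M as response but without a4 and a5, the difference is a1 at every visit and the trajectories are forced to be parallel.

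**5. Does another planned analysis supply the test?** Mean Differences assigns mixed MANOVA model 4 to hypothesis 3a and model 5 to hypothesis 3b. A mixed design does include group by time. However, those models are described as treatment versus control over six assessment periods, whereas the comparison here is by PMAD status and blood is drawn at three visits. As described, model 4 does not supply the PMAD-by-visit test.

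**The case against.** Four points can fairly be made for the plan.

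- **The wording may be open.** A condensed article that says the test will be done and refers to any relevant interactions has shown its intent, and the full terms may be in an analysis plan that is not shown. This has some force. But the bracket names two specific terms without *eg*, which the same section uses elsewhere for examples. On an open reading the needed term would be optional, and AIC or QIC selection could remove it. The article chose to specify the model, and the specification does not match the purpose stated just before it.
- **Aim 3 is partly covered.** A reader might infer that the whole aim lacks a trajectory test. The article does not support that: the mixed group-by-period analysis in Mean Differences addresses the smart versus traditional bassinet comparison, even though its six periods do not fit three blood draws. The gap is confined to PMAD status, a non-randomized comparison.
- **Hypothesis 3a is largely about levels.** It expects greater innate activity in women with PMADs in late pregnancy and at 3 and 6 months, and the cross-sectional models can show such differences. This stands. Separate comparisons by visit are still not a test that the difference changes.
- **The loss may be small.** A reader might also infer a quantified loss of power. None can be given. Such figures would have to assume the immune marker as response, which the article does not specify. They would also depend on the pattern chosen: patterns with no difference in pregnancy favor the interaction test, but hypothesis 3a expects a difference there.

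**Conclusion.** The point holds in a limited form. The longitudinal immune analysis is given a stated purpose that its listed model cannot serve: no term tests a changing PMAD versus no-PMAD difference in immune markers, and the response appears to be mood.

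The extent is one of the two comparisons in Aim 3. The randomized comparisons of sleep and mood are unaffected. The conclusion rests on two readings of the section: that group means PMAD status, and that mood is the GEE response. The first is well supported by the surrounding steps. The second rests on the phrase about within-women correlation of mood. If the immune marker were in fact the intended response, marker interactions on the predictor side would make no sense as listed, and group by visit would still be missing.

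**What to change.** Rewrite the longitudinal step in Statistical Analyses for Immune Measurements as follows.

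1. Make the immune marker, or the factor score from the planned data reduction, the response.
2. Include PMAD group, visit (late pregnancy, 3 months, 6 months) and group by visit, with the planned covariates. Name the 2-df group-by-visit test as the prespecified test of whether the group difference varies across the study period.
3. Keep that term whatever AIC or QIC selection suggests.
4. Report the group difference at each visit with a 95% CI from this model.
5. Keep the mood-on-marker models, with marker by group and marker by visit, as secondary analyses of association, and do not interpret those terms as a changing group difference.

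The cost is analysis-plan wording and two model parameters per marker or score. No new data, visits or assays are needed. Recruitment began in January 2025 and analysis is expected to finish by July 2028, so the change can be made before the data are analyzed.

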### Missing Data

Attrition in our prior studies has been approximately 15%, and we have accounted for that in our planned sample size. In addition, in our prior studies, we have missing biological data (due to incomplete blood draws) in about 7% of the visits; we anticipate similar rates in this study, which will use the same approach. Given the prospective nature of our study, we will carefully evaluate missingness. If identified, we will employ one of the two strategies to handle missing data. The first approach relies on a technical assumption of missing at random and involves inclusion of covariates related to missingness in all analyses. Full information maximum likelihood performs well under ignorable missing data conditions such as missing at random. A second strategy we will use is multiple imputation. Although this has the potential to yield biased estimates dependent on the nature of missingness [97], we will employ this approach to implement sensitivity analysis under plausible assumption of missing not at random to examine the robustness of our inference [98].

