#### Intention-To-Treat Analyses

Intention-to-treat analyses [81,82] will be conducted to understand the extent to which participants who satisfy the inclusion criteria for enrollment and are therefore randomized to one of the two conditions (intention-to-treat population) are similar to participants who provided complete data across the measurement rounds (actually treated sample). The purpose of intention-to-treat analyses is to scrutinize whether the conclusions drawn from the RCT remain robust even after considering participant attrition across time [81]. We will adhere to the recommended guidelines for performing multiple imputation on clinical research data [83].

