#### Mean Differences

Initial analyses will be performed to verify that the random assignment procedure successfully equalized participants between the treatment and control groups on the preintervention variables. Thus, MANOVA will compare these 2 groups on the entire set of preintervention baseline measures. A chi-square test will verify that both groups have the same distribution of infant boys and girls. As participants will be randomized to groups using a random number generator, baseline equivalency of the 2 groups is anticipated.

Six separate mixed 2 (treatment vs control) × 6 (assessment period) MANOVA models will be conducted. Specifically, to assess hypothesis 1a (aim 1), the model (model 1) will be applied to the infant sleep quality outcome measures. To address hypothesis 1b (aim 1), the analysis (model 2) will be applied to maternal postpartum sleep quality outcome measures. To evaluate hypothesis 2a (aim 2), the model (model 3) will be applied to the maternal postpartum depression outcomes. To examine hypothesis 3a (aim 3), the model (model 4) will be estimated on the measures involving peripheral cytokines, immune cells, and stimulated cytokine profiles. To examine hypothesis 3b (aim 3), the model (model 5) will be undertaken on the measures of T-cell dysfunction. Furthermore, to examine the exploratory aim, the model (model 6) will be estimated on the epigenetic biomarkers.

In each of the mixed MANOVA models, several follow-up analyses will be conducted to examine the results. First, a mixed (between-subjects and within-subjects) analysis of variance will be applied on each specific outcome. Second, independent 2-sided *t* tests will assess mean differences between the treatment and control group (at each timepoint) on each outcome. Third, dependent 2-sided *t* tests will permit scrutiny of the temporal change in mean scores between every 2 timepoints on every outcome. Fourth, the longitudinal trajectories across the entire 6-month period for both the treatment and control groups will be graphed using 95% CIs to provide a visual tool to offer insights to understand the effectiveness of the RCT.

Prior to conducting analyses, the normal distribution of all the measures will be inspected. If a variable is evidenced to be nonnormally distributed, then the bootstrapping variant of these statistical techniques instead will be performed to obtain corrected *P* values [84].

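### The missing-data rule lets arm comparisons be adjusted for data-chosen, possibly post-randomisation variables, because it does not separate auxiliary use from outcome-model adjustment

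*Protocol article*

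**What the plan says.** The Missing Data section says missingness will be evaluated and then: "If identified, we will employ one of the two strategies to handle missing data". The first strategy assumes data are missing at random and "involves inclusion of covariates related to missingness in all analyses". The sentence after it reads: "Full information maximum likelihood performs well under ignorable missing data conditions such as missing at random". The second strategy is introduced with "A second strategy we will use is multiple imputation" and is tied to sensitivity analysis under missing-not-at-random assumptions.

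Four other places bear on the point.
- The Intention-To-Treat Analyses section also plans imputation: "We will adhere to the recommended guidelines for performing multiple imputation on clinical research data".
- The Mean Differences section gives the arm comparisons: "Six separate mixed 2 (treatment vs control) × 6 (assessment period) MANOVA models will be conducted". These are followed by mixed analyses of variance for each outcome and independent t tests at each timepoint.
- The section on additional covariates lists items that arise after randomisation, among them "consistency of bedtime routine [71-73] and when moved to a crib".
- The Randomization section states that the study is not blinded.

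**The concern.** The rule gives a role (covariates), a selection criterion (related to missingness) and a scope (all analyses). It gives no restriction to pre-randomisation variables. This matters for three reasons.

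First, the set depends on who drops out, so the adjusted comparison is not fixed in advance, in a trial where allocation is known.

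Second, most of the observed data that could explain dropout are collected after randomisation. Table 1 schedules sleep and mood measures monthly through month 6. Hypothesis 2b says the bassinet acts on depression through infant and then maternal sleep. If poor sleep predicted dropout and were entered in the depression model, the analysis would adjust away part of the pathway the trial sets out to show.

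Third, the analyses named for the arm comparisons (MANOVA, ANOVA, t tests) have no step that accepts auxiliary variables as conventionally fitted. For those analyses, the literal way to include a covariate is to add it to the outcome model. Methods that assume missing at random need predictors of missingness in the imputation or likelihood step, and that does not require adjusting the arm effect for them.

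**Working it through.** **Inputs from the article (Power section).** Two-sided 5% level, 80% power. Effect sizes are d = 0.39 (infant sleep), 0.27 (maternal sleep quality) and 0.33 (depression). Stated totals are 208, 434 and 286. Allocation is 1:1.

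**The article's own figures.** Using n per arm = 2(1.960 + 0.842)²/d²:
- d = 0.39 gives 104 per arm, total 208.
- d = 0.27 gives 216 per arm, total 432.
- d = 0.33 gives 145 per arm, total 290.

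All are within 3% of the stated totals. These figures are not in dispute; they only anchor the illustration.

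**Assumptions not in the article.** The bassinet effect on depression is constant over visits. The within-arm correlation r between the selected covariate and the outcome is 0.3, 0.5 or 0.7.

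**Effect of adjustment.** Let the selected covariate itself be shifted by the bassinet by d_c, in SD units and in the beneficial direction. The adjusted arm difference is then d − r·d_c, with residual SD √(1 − r²).

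If the covariate is an earlier score with the same effect as the outcome (d_c = d = 0.33), the adjusted difference is 0.33(1 − r). Power is at the stated 286 women, 143 per arm:
- r = 0.3: 0.33 × 0.7 = 0.231. Divided by 0.954 this is 0.242, and power is 53%.
- r = 0.5: 0.33 × 0.5 = 0.165. Divided by 0.866 this is 0.191, and power is 36%.
- r = 0.7: 0.33 × 0.3 = 0.099. Divided by 0.714 this is 0.139, and power is 22%.
- Unadjusted: 0.33, and power is 80%.

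If the covariate is a sleep measure carrying the article's own effect sizes:
- Maternal sleep quality (d_c = 0.27): 0.33 − 0.27r = 0.249 at r = 0.3 and 0.141 at r = 0.7.
- Infant sleep (d_c = 0.39): 0.33 − 0.39r = 0.213 at r = 0.3 and 0.057 at r = 0.7.

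If the covariate is a baseline variable, randomisation makes d_c = 0 on average, and the difference stays at 0.33.

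**Simulation check.** 200,000 subjects, two visits, d = 0.33 at both, and about 13% dropout at the second visit depending on the first score. Estimated arm differences for r = 0.3 / 0.5 / 0.7:
- All data, no dropout: 0.32 / 0.33 / 0.34.
- Completers only, unadjusted: 0.32 / 0.32 / 0.32.
- First score as a covariate in the outcome model: 0.22 / 0.17 / 0.10.
- First score used only to impute the missing values: 0.32 / 0.33 / 0.34.

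The same variable recovers the full-data effect when used for imputation and attenuates it when used as a covariate. In this scenario the attrition bias itself is at most about 0.01 SD, far less than the 0.10 to 0.24 SD lost by adjustment.

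**The case against.** A reader might infer that the protocol has decided against auxiliary variables, that earlier depression or sleep scores will be covariates, and that the power losses above are to be expected. The article does not support this. The sentence on full information maximum likelihood directly follows the rule and is compatible with auxiliary use. Multiple imputation is planned in two places. No section names an earlier outcome as a covariate, the list of additional covariates contains no study outcome, and the mixed models already treat the monthly scores as dependent variables. The rule is also conditional and one of two strategies. Those objections stand, and they make the attenuation a what-if whose range starts at zero.

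It can also be said that choosing predictors of missingness is analysis-plan detail that an article may leave out. That is fair for the list of variables. It does not cover the rule itself, which the article does state and which, followed literally, permits adjustment for post-randomisation variables. Nor does the likelihood sentence settle the matter: it suits the structural equation models, but the arm comparisons are MANOVA, ANOVA and t tests. Treating repeated scores as dependent variables does not exclude sleep from a depression model or an earlier value from a follow-up comparison at one visit.

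Finally, there is overlap with the list of additional covariates, which already includes post-randomisation items. Restricting that list to baseline items would still leave the missing-data rule in force.

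**Conclusion.** The point holds as a defect in how the rule is worded. As written it allows arm comparisons to be adjusted for variables selected from the dropout pattern, including ones the bassinet may affect. With the section's expected attrition of about 15%, some missingness is likely, so one of the two strategies will probably be needed.

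The size depends on what is selected. With baseline variables only, there is no such bias, just a covariate set that is not fixed in advance. With an affected variable whose bassinet effect equals that on depression, the depression effect falls from 0.33 SD to between 0.23 and 0.10 SD, for assumed correlations of 0.3 to 0.7 and a constant effect. The power figures also rest on a two-group comparison at a single visit, which simplifies the planned repeated-measures models. They show what the wording permits and do not forecast what the trial will do.

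**What to change.** Reword the first strategy in the Missing Data section to say two things.
- Variables related to missingness, including post-randomisation measures, enter only as auxiliary variables in the multiple imputation (run by arm) or the full information maximum likelihood step.
- The models comparing arms keep the same prespecified baseline covariates whatever the missingness analysis shows.

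Because the section now links imputation to missing-not-at-random sensitivity analysis, add that imputation under missing at random also serves the MANOVA, ANOVA and t-test comparisons. This agrees with the imputation already planned in the Intention-To-Treat Analyses section.

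The change needs no new data and no change to sample size or schedule. The cost is a few sentences in the plan and slightly more analysis work.
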